### Outcome measures

The primary outcome of the trial is a change in cardiorespiratory fitness after the 14-week HIIT intervention. Secondary outcomes are changes in body composition, cardiovascular health and metabolic biomarkers of health, as well as measures of feasibility and physical activity and sedentary behaviour levels. Both primary and secondary outcomes will be measured before and after the 14-week intervention (Fig. 2).

Table 1 summarises the outcome measures to be made and the time points at which they will be measured during the study.

**Table 1 Tab1:** Indication of physiological variables measured and timepoints of each measurement

Variable	Timepoints measured
*Primary outcome*	
Peak VO_2_, HR at peak VO_2_, HR at 65 and 85% peak VO_2_	Baseline, post-intervention
*Secondary outcomes*	
Anthropometry	
Skinfolds	Baseline, post-intervention
Body mass and waist:hip	Baseline, every 4 weeks during intervention, post-intervention
Brachial blood pressure	Baseline, post-intervention
Central blood pressure and arterial stiffness	Baseline, post-intervention
Echocardiography	Baseline, post-intervention
Biomarkers of metabolic and cardiovascular health	Baseline, post-intervention
Feasibility (adherence and dropout rate)	Baseline, every 4 weeks during intervention, post-intervention
Accelerometry	Baseline, every 4 weeks during intervention, post-intervention

*VO*_*2*_*peak* Peak oxygen consumption, *HR* Heart rate

### Study procedures

#### Study visits

Volunteers will be required to visit the laboratory for an information session on the study. Eligible participants will then visit the laboratory to have their baseline and post-intervention measures taken. Participants in the exercising group will perform the HIIT program for 14 weeks in their own homes. During the intervention all participants will also visit the laboratory every 4 weeks (4th, 8th, and 12th weeks) to have an accelerometer fitted for measures of seven-day habitual activity. At these visits, body mass and waist-hip ratio will also be measured. Participants will be asked to refrain from consuming alcohol or caffeine for at least 24 h and food for at least 8 hours (eight-hour fast) before visiting the laboratory. Participants will also be asked to refrain from performing strenuous exercise 48 h prior to their measurement days. Post-intervention measurements will be performed a minimum of 48 h and a maximum of 4 days after the end of the HIIT intervention.

#### Randomisation

All eligible women will be classified as being in either one of two BMI groups (normal BMI: 20-24.9 kg/m^2^, *n* = 60; high BMI: 25-35 kg/m^2^, *n* = 60). Women will then be randomized into either a control group (CON) or a group that will follow the HIIT protocol (HIIT) resulting in four groups of women: high BMI control (CON-H; *n* = 30), normal BMI control (CON-N; n = 30), high BMI HIIT (HIIT-H; n = 30) and normal BMI HIIT (HIIT-N; n = 30). The randomisation procedure for the intervention groups will be done using Microsoft Excel RANDBETWEEN function. The RANDBETWEEN function (=RANDBETWEEN (1,2)) is able to assign participants into one of the two groups, in this instance 1 = CON and 2 = HIIT. Two random sequences of 120 numbers each (group 1 or 2) is generated for each BMI category (high and normal). The sequences were generated by an investigator who is not involved in the data collection procedures. Upon enrolment of a participant into the study, the group allocation of the participant is revealed to a non-blinded research assistant responsible for data collection.

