### Recruitment of participants

Volunteers will be recruited from the academic community of the University as well as from the surrounding central business district. Study advertising will be placed on the online University newsletter, social media platforms such as Facebook, through direct invitation by the research team via their teaching roles and posters with study information will be displayed throughout the University’s faculties. The expected time frame for recruitment of participants is anticipated to take 18–24 months. Eligible volunteers will be enrolled into the study as and when they volunteer. Participants will be compensated for their costs incurred travelling to the laboratory for assessments. Recruitment of participants started on 1st July 2018 and is ongoing, and data collection is in progress.

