#### Blinding

The researcher collecting data will not be blinded to the group in which each participant is allocated because they will take all pre-, during and post-intervention measures from the participants and will monitor adherence to the HIIT intervention for the duration of the 14 weeks. An investigator and/or statistician will analyse data that has had the group allocation labels removed.

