### Maximal exertion test and determination of the intensity of the home-based HIIT exercises

All participants will undergo a maximal exertion test for the determination of measures of cardiorespiratory fitness and to determine the relative intensity (heart rate and rating of perceived exertion) at which the HIIT intervention should be performed. The maximal exercise test will take place at the pre-intervention visit and at the end of the 14-week intervention. A progressive incremental exercise test to volitional fatigue on a motorised treadmill will be performed to determine maximal aerobic capacity (relative VO_2_peak). An exercise physiologist will monitor the test and test variables. The participants will first perform a five-minute warm up (0% gradient and self-selected speed). A Balke-Ware treadmill protocol will be used [53]. During the test the treadmill speed will stay constant at 5.3 km/h while the incline will increase by 1% every minute until the participant reaches exhaustion or the test is terminated. Participants will be required to wear a face mask (soft silicone for comfortable fit) during the test for the collection of expired respiratory gases. Breath-by-breath oxygen consumption and energy expenditure will be determined using a computerized analyzer (Quark ergo, COSMED, Rome, Italy). Heart rate will also be measured throughout the test using a wireless heart rate monitor connected to the same computerized analyzer. Rating of perceived exertion (RPE) will be monitored every 2 minutes during the test using the 6–20 Borg scale [54, 55]. The test will be terminated if the participant reaches volitional fatigue and/or if any of the test termination criteria appear as outlined in the American College of Sports Medicine (ACSM) test termination criteria [56]. The test will be considered a maximal effort if (i) the measured oxygen consumption does not increase by more than 150 ml per successive workload, (ii) a respiratory quotient (R) value equal to or above 1.15 is reached, (iii) heart rate is more than 90% of the age-predicted maximal heart rate and (iv) the RPE is above 19 on the 6–20 Borg scale. From the maximal exercise test, peak uptake of oxygen indexed to body mass (relative VO_2_peak in ml/min.kg^− 1^) will be obtained and heart rate and estimated RPE at 85% VO_2_peak_*,*_ and 65% VO_2_peak will be calculated to determine the intensities of the HIIT work phase and the HIIT active rest phase respectively.

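### As written, allocation reaches the unblinded data collector at enrolment, apparently before baseline testing, which leaves the baseline half of the primary outcome open to avoidable assessor bias

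*Protocol article*

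**What the plan says.** The Randomisation section sets the disclosure rule: "Upon enrolment of a participant into the study, the group allocation of the participant is revealed to a non-blinded research assistant", who is the person collecting the data. Recruitment of participants makes enrolment rolling: "Eligible volunteers will be enrolled into the study as and when they volunteer". Study visits mentions an information session and goes on: "Eligible participants will then visit the laboratory to have their baseline and post-intervention measures taken".

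The Blinding section states that the researcher collecting data is not blinded, "because they will take all pre-, during and post-intervention measures from the participants", and because the same person monitors adherence. Only the analysis is done with group labels removed.

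Under Outcome measures, "The primary outcome of the trial is a change in cardiorespiratory fitness after the 14-week HIIT intervention". The section on the maximal exertion test gives the timing, "The maximal exercise test will take place at the pre-intervention visit and at the end of the 14-week intervention", and the form of the test: "A progressive incremental exercise test to volitional fatigue on a motorised treadmill will be performed". It also has an exercise physiologist monitor the test, and does not say whether this is the unblinded assistant.

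**The concern.** With a single researcher, unblinded follow-up may be hard to avoid. Unblinded baseline measurement is not. When a test ends at volitional fatigue, the encouragement given can affect when it ends, and skinfolds are read by hand with callipers. If the person running the visit knows the arm, these readings can drift by arm without any intent.

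Because the primary outcome is a change from baseline, a reading that is too low in the HIIT arm appears as improvement, and one that is too high hides it. Removing labels for the analyst does not help, because the shift would already be in the data.

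**Working it through.** **1. Order of events.** Four statements bear on it:
- Enrolment happens when an eligible woman volunteers (Recruitment of participants).
- Disclosure happens at enrolment (Randomisation).
- Eligible women then attend for baseline measures (Study visits).
- Pre-intervention measures are among those taken by the unblinded researcher (Blinding).

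The first three give the order enrolment, disclosure, baseline. The fourth agrees with it. No sentence puts disclosure after baseline or provides a blinded baseline assessor.

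**2. Is the arm needed at baseline?** All participants do the same maximal test, controls included (Maximal exertion test; Control group). The HIIT heart-rate and exertion targets are calculated from that test, so HIIT instruction with those targets can only follow it. Adherence monitoring starts later still. Nothing at baseline needs the allocation.

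**3. The plan's own figure.** Inputs from Sample size determination: f = 0.20, correlation ρ = 0.50, alpha 0.05, power 85%, N = 60. For two groups and m = 2 measurements, the group-by-time test has noncentrality λ = N·f²·m/(1 − ρ) = 60 × 0.04 × 2/0.50 = 9.6, on 1 and 58 degrees of freedom. Power is 0.861; N = 58 gives 0.849. The stated 60 is reproduced.

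**4. The effect this implies.** The variance of change is 2σ²(1 − ρ) = σ² at ρ = 0.50. For a difference in change of δ SD with equal arms, λ = N·δ²/4. Setting 60·δ²/4 = 9.6 gives δ² = 0.64, so δ = 0.8 SD.

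**5. How a baseline shift passes through.** Suppose baseline in the HIIT arm reads b too low relative to control, with the final test unaffected.
- Difference in change: the true difference + b.
- Baseline-adjusted difference: the true difference + β·b, where β = ρ = 0.50 if the SDs are equal, so about half of b.

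**6. Illustration in outcome units.** The document gives no SD, so 4–6 ml/min/kg is assumed, and so is b = 1 ml/min/kg. The implied effect is 0.8 × 4 = 3.2 to 0.8 × 6 = 4.8 ml/min/kg.
- Difference in change: 1/4.8 = 21% to 1/3.2 = 31% of it.
- Baseline-adjusted: 0.5/4.8 = 10% to 0.5/3.2 = 16% of it.

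**7. Illustration for false positives.** With no true effect and an assumed shift of b SD, the test of difference in change has λ = N·b²/4 (for b = 0.2: 0.6 at N = 60, 1.2 at N = 120). Type I error at nominal 0.05:

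| Assumed b (SD) | N = 60 | N = 120 |
|---|---|---|
| 0.1 | 0.067 | 0.084 |
| 0.2 | 0.119 | 0.192 |
| 0.3 | 0.208 | 0.371 |
| 0.4 | 0.332 | 0.584 |

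The shift in step 6 is 1/6 = 0.17 to 1/4 = 0.25 SD. A larger sample makes this worse, because a systematic shift does not average out.

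**The case against.** The order is inferred. Enrolment is never defined relative to the baseline visit, the Blinding section describes one person's role over the whole trial, and the two figures that could settle the sequence are not shown. This stands as a limit on certainty. It does not supply a different order: the text ties disclosure to enrolment and nowhere delays it.

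The measurements are also better protected than a bare description suggests. Treadmill speed and incline steps are fixed, gas exchange is measured by a computerised analyser, and four criteria define a maximal effort. Blood pressure uses an automated monitor with a third-reading rule. Skinfolds are taken in duplicate with a 5% rule. The exercise physiologist may be someone other than the unblinded assistant. All of this narrows the room for bias. It does not close it, since the article does not say what happens to a test that misses the criteria, and the Blinding section still assigns all pre-intervention measures to an unblinded person.

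The size is illustrative. The protocol states f = 0.20, which it calls small; 0.8 SD is a conversion, and the shift and SD are assumed. That is correct, and the percentages are not an estimate of bias in this trial.

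A reader might also infer that women who learn they are controls could leave before baseline. The documents do not support this. The Randomisation section names only the assistant as recipient, and no sentence says when the woman learns her arm.

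**Conclusion.** The point holds as an avoidable risk of assessor bias in the baseline half of the primary outcome and in assessor-read measures such as skinfolds. It rests on the plain reading of the Recruitment, Study visits, Randomisation and Blinding sections, not on one explicit sentence.

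A reader might go further and infer that baseline VO2peak is in fact biased, or that adjusting for baseline would do nothing. Neither follows. The document contains no data on the matter, and adjustment would remove about half of a shift at correlation 0.50, under equal SDs. The sample size is not affected. The change is worth making because the stated rule creates a risk that nothing in the baseline procedures requires.

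**What to change.** For women still to be enrolled, reword the Randomisation section so that the investigator who generated the sequences, and who is outside data collection, holds the list. That investigator releases each allocation to the assistant and the participant only after all baseline measures, including the maximal test, are complete and entered. HIIT instruction then follows. Amend the Blinding section to say that baseline measures are taken before the arm is known. If this is already the practice, correct both sections to describe it, and state whether the exercise physiologist knows the arm.

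The cost is small: no extra participants, measurements or staff. Baseline accelerometry takes a week before the intervention, so instruction may have to wait for it if it is now given on the day of the maximal test.

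Two limits remain. Recruitment began on 1 July 2018, was expected to take 18–24 months and was about 18 months in when the article appeared on 30 December 2019. Women already enrolled came in under the current rule, so the date of the change should be recorded and reported. The post-intervention test also stays unblinded, and that should be stated as a limitation.

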#### Blinding

The researcher collecting data will not be blinded to the group in which each participant is allocated because they will take all pre-, during and post-intervention measures from the participants and will monitor adherence to the HIIT intervention for the duration of the 14 weeks. An investigator and/or statistician will analyse data that has had the group allocation labels removed.

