#### Cardiovascular health measures

##### Brachial blood pressure

Resting brachial blood pressure (BP) will be measured prior to any testing or exercise after a five-minute rest period. The average of two measurements will be taken with an automated BP monitor (SpaceLabs, Redmond, WA). If the first two measures for either the systolic or diastolic blood pressures differ by more than 5 mmHg, a third measurement will be taken to determine the mean blood pressure.

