##### Central blood pressure and arterial stiffness

Pulse wave velocity (PWV), aortic reflected wave index, central aortic BP and its determinants (reflected and forward wave pressures) will be determined using commercially available hardware and software. After resting for 15 min in the supine position, the radial waveform will be recorded by applanation tonometry. A high-fidelity SPC-301 micromanometer (Millar Instrument, Inc., Houston, Texas), interfaced with a computer utilizing SphygmoCor software, version 9.0 (AtCor Medical Pty. Ltd., West Ryde, New South Wales, Australia) will be employed. The waveform will be calibrated by auscultatory measurement of the brachial BP. From the radial pressure waveform signal the SphygmoCor software calculates the aortic pressure waveform by means of a validated generalized transfer function. Aortic pulse pressure and central to brachial pulse pressure amplification ratio (PPamp) will be calculated. The magnitude of the forward and reflected wave components of the aortic pressure waveform will be determined by wave separation analysis using a modified triangular waveform (SphymoCor software). Aortic PWV will be measured by sequential recordings of the arterial pressure waveform at the carotid and the femoral arteries. Aortic PWV will be calculated as the ratio of the distance in meters to the transit time in seconds.

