##### Echocardiography

Echocardiographic measurements will be performed using an ultrasound (Acuson S2000, Siemens Healthcare GmbH, Germany) with the participant in the partial left decubitus position. Left ventricular (LV) dimensions will be determined using two-dimensional directed M-mode echocardiography in the short axis view and these recordings will be analysed according to the American Society of Echocardiography convention. M-mode images will be obtained perpendicular to the posterior wall and as close to the mitral leaflet as possible without images of the mitral leaflet appearing. The interventricular septal wall thickness (IVS), posterior wall thickness (PWT) and internal dimensions of the left ventricle will all be measured at both end diastole and end systole. Left ventricular diastolic function will be assessed using pulsed wave Doppler by assessing the mitral inflow at rest in the apical four chamber view. Pulse wave Doppler recordings of transmitral velocity will be obtained during early (E) and late (atrial-A) periods of left ventricular diastolic inflow, and expressed as the E/A ratio. Tissue Doppler imaging (TDI) will be used to measure the motion of the mitral valve annulus in the apical four-chamber view. The peak relaxation velocities during early (e’) and late (atrial) (a’) diastole will be obtained. Measures of left ventricular diastolic function will be expressed as the E/e’ ratio and the ratio of early to late mitral annular velocity (e’/a’). Cardiac systolic function will also be assessed by using two-dimensional speckle tracking derived myocardial deformation (strain and strain rate). Speckle tracking analysis will be performed on parasternal short axis images for circumferential strain and apical four chamber images for longitudinal strain. Peak strain and peak strain rate will be recorded.

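### The unblinded adherence monitor also takes all week-14 measures, including the effort-dependent primary test, and label removal at analysis cannot correct bias that arises at measurement

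*Protocol article*

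**What the plan says.** Four parts of the protocol article bear on this.

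- **Who knows the allocation.** Under Randomisation, on enrolment "the group allocation of the participant is revealed to a non-blinded research assistant responsible for data collection". The Blinding section confirms this: "The researcher collecting data will not be blinded to the group in which each participant is allocated". It also explains why: "they will take all pre-, during and post-intervention measures from the participants and will monitor adherence to the HIIT intervention".
- **What is blinded.** The same section gives one protection: "An investigator and/or statistician will analyse data that has had the group allocation labels removed".
- **How the primary outcome is obtained.** The maximal exertion section says: "A progressive incremental exercise test to volitional fatigue on a motorised treadmill will be performed". Speed and incline steps are fixed, gas exchange is read by a computerised analyser, and four criteria define a maximal effort. An exercise physiologist monitors the test.
- **Secondary measures that involve judgement.** For echocardiography, "these recordings will be analysed according to the American Society of Echocardiography convention". For tonometry, "The waveform will be calibrated by auscultatory measurement of the brachial BP", whereas for resting brachial pressure "The average of two measurements will be taken with an automated BP monitor".

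The limitations in the Discussion cover compliance and the lack of heart rate monitors. They do not mention unblinded assessment.

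**The concern.** Participants cannot be blinded to exercise versus no exercise, so protection at the point of measurement is the main safeguard left. The plan provides none there. The tester knows each woman's arm, has followed the HIIT women's adherence for 14 weeks, and then runs a test whose end point depends on effort. More encouragement, or a later stop, in one arm would raise VO2peak in that arm. In the data this would look the same as a training effect.

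Removing labels before analysis protects the choice and reporting of analyses. It does not change a value already recorded under knowledge of the arm.

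The reason given for not blinding describes how the work is shared out. It does not show that no protection is possible.

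**Working it through.** **Step 1: follow each measure from acquisition to analysis.**

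| Stage | Who, according to the article | Blinded? |
|---|---|---|
| Allocation revealed | Research assistant who collects the data | No |
| Adherence monitoring | Researcher collecting data | No |
| Treadmill test | Exercise physiologist monitors; the Blinding section gives all measures to the data collector | Not stated for the physiologist; no for the data collector |
| Echo and tonometry acquisition | Covered by the same wording on all measures | No |
| Reading of echo recordings | Reader not named | Not stated |
| Statistical analysis | Investigator and/or statistician | Yes, labels removed |

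The Discussion says that an exercise physiologist also takes the first HIIT session with participants. Even if that role is a different person from the data collector, nothing suggests the role is blinded.

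**Step 2: the plan's own figure.** The point does not rest on the sample size, but the illustration below uses its inputs, so I checked them. Inputs from Sample size determination: f = 0.20, correlation 0.50, alpha 0.05, power 85%, total 60. For a two-group, two-time within-between interaction:

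- λ = f² × N × m / (1 − ρ) = 0.04 × 60 × 2 / 0.5 = 9.6, with 1 and 58 degrees of freedom.
- Power = 0.861, and 60 is the smallest even total that reaches 0.85. The stated figure reproduces. The plan then doubles it to 120, or 60 per arm.
- On this reading the planned difference in change, d, in outcome SDs, solves N × d² / (4 × 2(1 − ρ)) = λ. So 60 × d² / 4 = 9.6 and d = 0.8.

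**Step 3: what an artefact would do.** The document gives no bias size, so b is assumed. With ρ = 0.5 the SD of change is √(2(1 − 0.5)) = 1 outcome SD. With 60 per arm the standard error of the difference in mean change is √(2/60) = 0.183 SD. If training had no effect, the rejection rate would be P(|Z + b/0.183| > 1.96).

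- b = 0.1: shift 0.548; P(Z > 1.412) + P(Z < −2.508) = 0.079 + 0.006 = 0.085.
- b = 0.2: shift 1.095; P(Z > 0.865) + P(Z < −3.055) = 0.194 + 0.001 = 0.195.

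A noncentral t calculation over a wider range gives:

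| Assumed b (SD) | N = 60 | N = 120 |
|---|---|---|
| 0.05 | 5.4% | 5.8% |
| 0.10 | 6.7% | 8.4% |
| 0.20 | 11.9% | 19.2% |
| 0.30 | 20.8% | 37.1% |

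A larger trial does not help: a fixed bias counts for more as the standard error shrinks. For scale, 0.1 SD is one eighth of the planned difference (0.1 / 0.8) and 0.2 SD is one quarter.

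**Step 4: which measures are exposed.** VO2peak is exposed through encouragement, the stopping point and the off-line derivation of the peak. Echo and strain are exposed at acquisition and at reading. The calibration pressure enters the central pressures. It does not enter aortic pulse wave velocity, which the article computes as distance over transit time.

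**The case against.** The strongest reply has four parts.

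- **The choice is disclosed and explained, and nothing contradicts it.** That is true. This is a risk of bias, not an error in the text. Disclosure does not reduce the risk, however, and the limitations omit it.
- **The treadmill test already has protections.** It has a fixed protocol, an automated analyser, published termination criteria and a four-part definition of maximal effort. This largely stands: a test that meets all four criteria leaves less room for encouragement to matter. It does not close the gap, because the article does not say what follows when the criteria are not met.
- **Coding of files, an averaging rule and an encouragement script are operating details that a condensed article may leave out.** This stands as far as it goes. A reader might infer that echo recordings will be read with the arm known. The article does not say so, and label removal may already reach that step. The point rests instead on what the article does fix: unblinded collection of all measures, with blinding stated only for analysis.
- **Changing methods in a running trial has its own cost.** This stands for calibration. Recruitment began on 1 July 2018 and data collection is in progress, so a switch from auscultation to the automated monitor could give a woman one method at baseline and another at week 14.

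Two further inferences are not supported. Auscultation does not compromise arterial stiffness as a whole, since pulse wave velocity does not use the calibration pressure. An error in a heard pressure also does not in itself favour HIIT: it biases the comparison only if it differs by arm, and otherwise it is noise.

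**Conclusion.** The point holds as a risk of measurement bias that the plan leaves open and could reduce cheaply. As written, one unblinded person who also monitors adherence takes all post-intervention measures, the primary one depends on effort, and the stated blinding starts too late to help.

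The size is unknown. The figures of about 8.5% and 19% rest on assumed artefacts of 0.1 and 0.2 SD, 60 women per arm, the plan's correlation of 0.5 and a simple comparison of changes. They show sensitivity and do not estimate the bias in this trial. A reader might infer that a positive VO2peak result would be an artefact. The document does not support that: it gives no evidence that testers treat the arms differently, and the analyser and effort criteria restrain how far they could move the result.

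That the data collector personally runs the treadmill test, the echo and the auscultation is inferred from the statement that this person takes all measures. A separate operator is possible, but none is described as blinded.

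**What to change.** 1. **Treadmill test.** Use one scripted encouragement text at fixed stages, identical for both arms and both visits. Keep the baseline results from the tester at week 14.
2. **Off-line derivation and reading.** Extend the planned label removal to stored gas-exchange files and to echo and strain recordings. Give each file a participant-visit code. Compute VO2peak by one fixed averaging rule. Have the echo recordings read in random order by the existing label-blind investigator, not by the person who acquired the images. Recordings already collected can be included where they were kept.
3. **Reporting.** Add unblinded acquisition to the limitations.
4. **Optional: tonometry calibration.** The automated monitor could supply the calibration pressure. This concerns central pressures only, and should apply only to women for whom baseline and week 14 can use the same method. The reading should be taken at tonometry, because that procedure follows 15 minutes supine whereas the brachial measurement follows a five-minute rest.

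The cost is a one-page script plus data-handling and reading time for existing staff. This assumes that the label-blind role is filled by an investigator able to read echo, since the article allows an investigator and/or a statistician. Image acquisition would stay unblinded, and participants would still know their arm, so the risk is reduced and not removed.
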